### Recruitment {15}

Patients will be recruited at Cardiac Surgery Division of each Participating Centre. Every patient fulfilling the eligibility criteria, after the signature of the informed consent, will be enrolled and randomized to one of the three groups of treatment. Recruitment will continue until the expected total number of patients is reached.

## Assignment of interventions: allocation

### Sequence generation {16a}

The list of randomization will be generated for each centre using STATA statistical software 14, by the Clinical Research Unit of Azienda Ospedaliera Universitaria Integrata of Verona. The balanced block randomization method will be used. To reduce predictability of a random sequence, details of any planned restriction will be provided in a separate document that is unavailable to those who enrol participants or assign interventions

### Concealment mechanism {16b}

Use of a validated password website will ensure concealment.

### Implementation {16c}

After a first researcher takes the informed consent forms, a second researcher will use the list of randomization to allocate the patient to one of the study arms. The study group will be revealed at the same time to the patient, the researchers, the first operator and the operating room staff.

## Assignment of interventions

### Who will be blinded {17a}

The researcher at the time of the informed consent and the data analyst will be blinded. Data is e-data so there are no outcome assessors.

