### Postoperative

- POD at arrival in intensive care unit (ICU), POD 1 and 4Blood chemistry samplesCalculation of eGFR (according to MDRD)ABG at arrival in ICU, at 3–6–12–24 h after surgery. Data collection on serum lactates, pH, paO_2_, paCO_2_, BE, HCO_3_−, calculation of the Pa/Fi ratioChest X-ray and evaluation of eventual pulmonary damage through Murray “Lung Injury Score” (LIS) [23]. The score considers 4 criteria for the development of ALI/ARDS: hypoxemia, respiratory system compliance, chest radiographic findings and the positive expiratory pressure level. Each criteria receives a score from 0 to 4 according to the gravity of the condition. The final score is obtained dividing the collective score by the number of components used. A score equal to 0 shows the absence of pulmonary damage, a score between 1 and 2.5 shows a mild to moderate pulmonary damage and a final score major than 2.5 shows the presence of ARDS.Monitoring of estubation time (hours)Calculation of VISmaxMonitoring of postoperative cardiac function at POD 4 through echocardiogram and evaluation of LVEFMonitoring of postoperative stroke; a diagnosed stroke by a neurologist according to clinical, radiological (CT scan and/or MRI) and electrophysiological examination (EEG). Patients affected by stroke will undergo “modified Rankin Scale” (mRS) calculation which evaluates the degree of disability following a stroke and will be compared to the preoperative mRS. The score goes from a minimum score of 0 (no disability) to 6 (death).Evaluation of acute kidney injury according to the definition of “Acute Kidney Injury” (AKIN) [27] through a stratification of renal damage in three stages: [1] Creatinine × 1.5–2.0 from baseline or Creatinine increased by at least 0.3 mg/dl (26.5μmol/L) [2]; Creatinine × 2.0–2.9 from baseline [3]; Creatinine > 3.0 from baseline or Creatinine increased at least 4 mg/dl (353.6 μmol/l) or the initiation of dialysis.Monitoring of gastrointestinal ischaemia: a diagnosed ischaemia by a surgery consultant according to the value of serum lactate, WBC, clinical and radiological (CT scan and/or abdomen ultrasound) examination.Monitoring of in-hospital death

- Follow-up visit at 30 days from surgery:Stroke and eventual transitory or permanent neurological damage (mRS score)Acute kidney injury (eGFR and AKIN score)Cardiac function (LVEF)Re-hospitalizationDeath for cardiovascular or other causes.

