### Procedure for unblinding if needed {17b}

Randomization is communicated to the patients and to the investigators.

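### The protocol says there are no outcome assessors, yet several secondary outcomes rest on clinical judgement and nothing keeps those who judge unaware of the arm

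*Protocol article*

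**What the plan says.** Under Who will be blinded {17a}, the protocol article names two blinded roles: "The researcher at the time of the informed consent and the data analyst will be blinded". It then closes the question of outcome assessment: "Data is e-data so there are no outcome assessors".

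On disclosure, Implementation {16c} states: "The study group will be revealed at the same time to the patient, the researchers, the first operator and the operating room staff". Procedure for unblinding if needed {17b} adds: "Randomization is communicated to the patients and to the investigators".

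The Postoperative part of Procedures describes how the clinical outcomes arise. Stroke is "a diagnosed stroke by a neurologist according to clinical, radiological (CT scan and/or MRI) and electrophysiological examination (EEG"). Gastrointestinal ischaemia is "a diagnosed ischaemia by a surgery consultant according to the value of serum lactate, WBC, clinical and radiological" examination. Patients with stroke receive an mRS score, "which evaluates the degree of disability following a stroke and will be compared to the preoperative mRS". The same part has a chest X-ray feeding the LIS and an echocardiogram on postoperative day 4 for LVEF. mRS and LVEF are assessed again at the 30-day visit. All of these appear among the secondary outcomes in Outcomes {12}.

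**The concern.** Electronic storage describes where a result is kept, not how it came about. A stroke diagnosis retrieved from the hospital system is still a neurologist's judgement, and a stored ejection fraction is still someone's reading of an echocardiogram. By reasoning that electronic data leave no assessors, the protocol removes the question of whether those assessors should know the arm.

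At stake is detection bias in the secondary outcomes that depend on judgement. Knowledge of the arm can influence how an ambiguous deficit is classified, how disability is graded, how an infiltrate is scored, or whether abdominal findings are called ischaemia. The abstract presents major postoperative complications related to organ malperfusion as part of the secondary outcome set. They are what would give a lactate difference clinical meaning.

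**Working it through.** No figure in the plan depends on this point, so the check sets the sections side by side.

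**Step 1: are there assessors?** For each clinical secondary outcome, from the Postoperative procedures:

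| Outcome | How it is obtained | Assessor named? |
|---|---|---|
| Stroke | Clinical, radiological and EEG examination | Yes, a neurologist |
| Gastrointestinal ischaemia | Lactate, white cells, clinical and radiological examination | Yes, a surgery consultant |
| mRS (0–6) | Graded disability, compared with the preoperative score | No; a rater is implied |
| LIS | Four criteria scored 0–4, one from the chest X-ray | No; a reader is implied |
| LVEF | Echocardiogram on day 4; again at 30 days | No; a reader is implied |

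Two assessors are named outright, and three more follow from the nature of the measure. The statement in {17a} cannot stand beside this.

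**Step 2: are they kept unaware of the arm?** {17a} blinds the researcher at consent and the data analyst. {16c} and {17b} tell the patient, the researchers or investigators, the first operator and the operating room staff. The assessors in step 1 are on neither list. They are not told by design and not protected by design: they can learn the arm from the patient, a colleague or a request form.

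**Step 3: could they be unaware?** Under Intervention description {11a}, the pressure target applies during bypass, after general anaesthesia has been given. No section gives the neurologist, the surgery consultant or an image reader a task that needs the allocation. The Preoperative procedures measure baseline MAP in every patient whatever the group, so that step does not reveal the arm.

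**Step 4: which outcomes are reached?** The primary endpoint in Outcomes {12} is peak serum lactate during bypass, a laboratory value. Lactate AUC, lactate above 3 mmol/l, blood gases and NIRS are also measured rather than judged. AKIN stage rests mainly on creatinine, and death needs no grading. The exposed outcomes are those in the table. Exposure within them is partial: stroke and gut ischaemia also rest on imaging, the mRS applies only to stroke patients, and the X-ray is one LIS criterion of four. Because the LIS divides the total by the number of components used, a one-grade difference in reading the film moves a four-component score by 1/4 = 0.25. That shows how much weight one reading carries; it is not an estimate of bias.

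**Step 5: can the bias be sized?** No. The document gives no expected event rates for this population and no misclassification rates.

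**The case against.** The sentence in {17a} has a milder reading. The procedures are described as standard of care, and Plans for assessment and collection of outcomes {18a} has the data retrieved from the hospital information system. The authors may mean only that the trial appoints no dedicated assessors. That is plausible, but it does not answer the point: routine clinicians then become the assessors, and whether they know the arm is still not addressed.

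The reach is also limited. The trial calls itself exploratory, its primary endpoint is a laboratory value, and several secondary outcomes are objective. This stands, and it confines the point to the outcomes listed above.

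Four stronger readings are tempting but not supported:

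- **Everyone is told the arm.** The analyst is blinded, and the neurologist, consultant and image readers are not on the disclosure list. What can be said is that nothing keeps them unaware.
- **Expected stroke counts can be derived from the 1.1% and 7.0% in the Background.** These are the two arms of one single-centre comparison (P=0.09), not rates expected here.
- **Clinicians lean in a known direction.** The Background describes conflicting evidence without consensus, so no direction can be assumed.
- **Patients, too, must be kept unaware.** No patient-reported outcome is listed. In an open trial that has recruited since 2021, withholding the arm from patients, or changing who runs the 30-day visit, is a debatable design choice rather than a correction.

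**Conclusion.** The point holds in a limited form. The claim that there are no outcome assessors is contradicted by the protocol's own procedures, and no section keeps the assessors of stroke, gastrointestinal ischaemia, mRS, chest X-ray and LVEF unaware of the arm. Followed as written, the plan leaves these secondary outcomes open to detection bias of unknown size and direction.

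A reader might infer that the primary comparison is compromised; it is not. Peak lactate, creatinine-based AKIN stage and death are largely unaffected, and the sample size, alpha and power are not involved.

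The conclusion assumes that mRS, the chest X-ray score and LVEF are rated by a person, since the document names the assessor only for stroke and gastrointestinal ischaemia. It also assumes that at least some of these raters work outside the theatre team, which the document does not state.

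**What to change.** Replace the sentence in {17a} with a statement that the neurologist, the surgery consultant and the readers of chest X-ray and echocardiogram assess unaware of the arm. Include the mRS rater wherever that person is not a member of the theatre team. Leave the arm off the referral and imaging requests these clinicians receive.

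The cost is wording and a local instruction at each centre. No extra reader is needed, and sample size, alpha and power do not change. There are three downsides:

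- Blinding will be imperfect, because the arm may sometimes be inferred from the chart or disclosed by the patient.
- The change must be notified as an amendment under the section on communicating protocol amendments {25}.
- Recruitment began on 02/05/2021 and is expected to end on 31/12/2026 (Trial status), so only patients still to be enrolled are covered. The report should state the date from which assessment was blinded.

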### Procedure for unblinding if needed {17b}

Randomization is communicated to the patients and to the investigators.

## Data collection and management

### Plans for assessment and collection of outcomes {18a}

All preoperative, intraoperative and postoperative procedures are standard of care in each Cardiac Surgery Division. The data collection will take place during the patient hospitalization by the research team in a dedicated datasheet. All the data are listed in the protocol and will be retrieved from the Hospital health information system. A separated datasheet with the same coding will be used for the participating centres. At the end of the study, all datasheets will be unified in a unique database and analysed by the promoting centre.

### Plans to promote participant retention and complete follow-up {18b}

The 30-day outpatient visit will be planned at the time of patient’s discharge.

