## Introduction

### Background and rationale {6a}

Most of cardiac surgery operations require a bloodless operating field and a steady heart (i.e. cardioplegic arrest). To ensure the perfusion of peripheral organs during the cardioplegic arrest time, the cardiopulmonary bypass (CPB) is installed. The CPB is a biomedical device, also named Heart-Lung machine, that, through a circuit, filtrates and oxygenates the venous blood of the patient, giving it back as arterial blood through a mechanical pump. The target blood flow during CPB is traditionally determined according to body surface area (BSA) and temperature. Under moderate hypothermia-to-normothermic conditions, the pump flow rate is set between 2.2 and 2.8 l/min/m^2^ by the majority of perfusionists [1]. Therefore, the CPB provides continuous blood flow, so the pressure produced is a “mean arterial pressure” (MAP). The MAP can be modulated by vasoactive and/or anaesthetic drugs, in order to maintain an appropriate perfusion pressures in all end-organs, particularly the kidneys, the brain and the gastrointestinal tract, avoiding tissue hypoperfusion and hypoxia. The latter, indeed, may occur in the postoperative period as organ damage: cerebral ischaemia and consequently transitory or permanent neurological injury [2], renal ischaemia and consequently acute kidney injury [3, 4], or gastrointestinal ischaemia [5, 6]. Therefore, the hypoperfusion during CPB could directly affect the morbidity and mortality of cardiac surgery. Consequently, the management of MAP acquires a crucial role. A value of 50–60 mmHg has been historically accepted as the “gold standard” MAP, according to the pioneering animal experiments and investigations of the dawn of cardiac surgery (around ‘50s) [2, 7–11]. However, in the last decades, the CPB has remarkably changed thanks to the evolution of technology and the availability of new biomaterials. Therefore, as highlighted by the latest European Guidelines [1], the current management of CPB can no longer refer to those pioneering studies. To date, only few authors focused their attention on the correlation between MAP values during CPB and cardiac surgery outcomes. Vedel et al. [12] compared the “high-target” MAP (70–80 mmHg) to “standard” MAP (50–60 mmHg) in terms of new postoperative cerebral injuries. They reported a higher incidence of stroke (7.0% vs 1.1%; *P*=0.09) and mortality (4.1% vs 0%; *P*=0.06) in the “high-target” MAP population compared to the “low-target” group. Conversely, Gold et al. [13] reported a reduction (from 12.9 to 4.8%) of major cardiac and neurologic events in patients treated with higher MAP compared to patients treated with the “standard” MAP during coronary artery bypass graft surgery (CABG). However, the abovementioned studies are both from a single institution, with small and selected sample sizes (i.e. CABG). Finally, Charleson et al. [14] compared the “high MAP” (80 mmHg) with “patient-tailored” MAP (comparable to pre-operative MAP of the single patient). The study showed no differences in terms of major cardiac and neurologic events (11.7 and 12.6% respectively). However, also this study included only patients undergoing CABG surgery. However, all the these investigations showed conflicting evidences, without achieving a real consensus on what should be the most adequate MAP target during CPB.

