#### Secondary objectives

To assess the intraoperative outcomes, through the following perfusion parameters:Intraoperative cerebral perfusion (through monitoring of the NIRS values)Intraoperative pulmonary perfusion (through Pa/FiO_2_ ratio, paO_2_, paCO_2_ at blood gas analysis, and VO_2_R and DO_2_ at CDI® Blood Parameter Monitoring System 550)

To assess postoperative clinical outcomes, through the following parameters:Intraoperative and postoperative low cardiac output syndrome (according to the values of vasoactive inotropic score, VIS) [22]Postoperative cardiac function (measuring left ventricular ejection fraction, LVEF)Postoperative respiratory failure (through the values of Lung Injury Score, LIS, scale) [23]Postoperative stroke and entity of transitory or permanent neurological damage (through score of modified Rankin Scale—mRS) [24]Postoperative acute kidney injury (through AKI score)Postoperative hepatic failure (measuring the hepatic function and coagulation indices)Postoperative gastrointestinal ischaemiaPostoperative cardiovascular death, or death due to other causes

To assess clinical outcomes at 30 days from surgery:Stroke and entity of the transitory or permanent neurologic damage (mRS score)Acute kidney injury (AKI score)Cardiac function (LVEF)Re-hospitalizationDeath for cardiovascular or other causes

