### Data management {19}

All data will be retrieved from electronic patient records at the time of hospitalization and then at the follow-up visit and collected in a dedicated anonymized datasheet. Informed consent and end-of-trial dates will be recorded in the electronic patient dossier, and signed paper forms will be stored within each hospital in a locked room, whose keys will only be available to the research team and will be safeguarded by the principal investigator.

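### Day-30 outcomes are taken from hospital electronic records and one outpatient visit with no stated route for non-attenders, so events first occurring after discharge may be missed

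*Protocol article*

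**What the plan says.** The protocol article describes how day-30 data are obtained in four places.

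- Plans for assessment and collection of outcomes {18a} places data collection in the hospital stay and says: "All the data are listed in the protocol and will be retrieved from the Hospital health information system".
- Data management {19} adds the visit: "All data will be retrieved from electronic patient records at the time of hospitalization and then at the follow-up visit".
- Plans to promote participant retention and complete follow-up {18b} consists of one sentence: "The 30-day outpatient visit will be planned at the time of" discharge.
- Procedures, Postoperative, under "Follow-up visit at 30 days from surgery", lists stroke with mRS, acute kidney injury, LVEF, re-hospitalisation and death. The Secondary objectives give the same five items under "To assess clinical outcomes at 30 days from surgery".

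The missing-data section {20c} names inverse probability weighting and last observation carried forward, with sensitivity analysis.

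Background {6a} says that perfusion must be maintained in "particularly the kidneys, the brain and the gastrointestinal tract". Kidney and brain are on both day-30 lists; the gut is on neither. Its entry, "Monitoring of gastrointestinal ischaemia: a diagnosed ischaemia by a surgery consultant according to the value of serum lactate" and other findings, stands in the block for ICU arrival and postoperative days 1 and 4. The Secondary outcomes label it postoperative only, while LVEF and kidney injury are labelled postoperative and 30-day.

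**The concern.** Attendance at the visit depends on the outcome being measured. A patient who has died cannot attend, and one disabled by a stroke or admitted to another hospital is less likely to. The stated sources are the visit and hospital electronic records, so a post-discharge event in a non-attender has no stated way into the dataset.

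The missing-data plan could turn that gap into a wrong value. A patient discharged event-free and then lost has event-free as the last observation, and carrying it forward records no event. Inverse probability weighting does not repair this if non-attenders have already been coded as event-free, or if the unobserved event is itself why they stayed away.

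The background cites a trial of high against standard MAP with stroke 7.0% vs 1.1% and mortality 4.1% vs 0%. At 300 per group, 4.1% is about 12 deaths (0.041 × 300 = 12.3), so a few missed deaths would matter to the reading of a safety comparison.

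**Working it through.** **The plan's own figures.** The article gives no day-30 attendance rate, no expected day-30 event rate and no split of events before and after discharge. Its one sample-size calculation concerns peak lactate during bypass. With difference 0.19, SD 0.7, two-sided alpha 0.01667 and 80% power, the two-sample formula gives 285 per group; dividing by the Mann-Whitney efficiency of 0.955 gives 299, against 300 stated. Nothing in it depends on day-30 capture, so what follows is illustration on stated assumptions.

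**Step 1: share of visit-dependent events missed.** Assume 10% do not attend (borrowed from the drop-out allowance in Sample size {14}) and that their post-discharge event rate is k times that of attenders.

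- If non-attenders are counted as event-free, the share missed is 0.1k / (0.9 + 0.1k).
- If only attenders are analysed, the rate is understated by 1 − 1 / (0.9 + 0.1k).

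| k | Counted as event-free: share missed | Attenders only: rate understated by |
|---|---|---|
| 1 | 10% | 0% |
| 2 | 18% | 9% |
| 3 | 25% | 17% |
| 5 | 36% | 29% |

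**Step 2: restrict the loss to post-discharge events.** In-hospital death and stroke are recorded during the stay (Procedures, Postoperative). Let f be the share of 30-day events that first occur after discharge and a the share of those that go unseen. With non-attenders coded event-free, observed rate = true rate × (1 − f·a). For an assumed true rate of 5%:

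| f | a = 30% | a = 50% |
|---|---|---|
| 100% | 3.5% | 2.5% |
| 50% | 4.25% | 3.75% |
| 25% | 4.6% | 4.4% |

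The first row assumes that no event occurs in hospital. It is a ceiling for death and stroke. Re-hospitalisation is by nature post-discharge, so for that outcome f is 100%.

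**Step 3: effect on a comparison.** Take the cited stroke rates, 7.0% vs 1.1%, with 300 per group and a pairwise two-sided test at 0.05 (normal approximation, rough at so few events). Let m = f·a be the share of all events lost, equal in both arms. The observed difference is 5.9 × (1 − m) points.

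| m | Difference (points) | Power |
|---|---|---|
| 0 | 5.9 | 96% |
| 10% | 5.3 | 94% |
| 30% | 4.1 | 86% |
| 50% | 3.0 | 73% |

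A value of m = 10% arises, for example, from f = one third and a = 30%. With a no higher than 50%, m = 50% needs every stroke to be post-discharge. The article does not say when the cited strokes occurred.

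**Step 4: the gut.** The Secondary objectives, the Postoperative procedures and the Secondary outcomes agree that gastrointestinal ischaemia is not a day-30 outcome. After discharge, two routes remain: the rule in {22} that all adverse events during the study are registered, and a re-hospitalisation entry for which no cause is specified. Neither involves an active assessment.

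**The case against.** The strongest reply is that this is a condensed article. The full protocol is a separate document, available on request, and tracing of non-attenders is the kind of detail an article leaves to it. The absence of a telephone procedure would indeed be no finding by itself. What stands against the reply is that the article does fix the route: two sections say all data come from hospital electronic systems, during the stay and at the visit, and the section on complete follow-up offers only a booking.

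Several stronger readings are tempting, and the article does not support them.

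- A reader might infer that events outside the treating hospital leave no trace in its records. The article does not say whether those systems link to other hospitals or to a death register.
- A reader might infer that a quarter to a half of all day-30 events are lost. That applies assumed missed-visit fractions of 30% to 50% to every event, including the deaths and strokes recorded in hospital. It is an assumption-based ceiling.
- A reader might infer bias between arms. That needs the loss to differ by arm, which nothing shows.
- A reader might infer that death, stroke and readmission are the only post-discharge safety outcomes, or that gut ischaemia is dropped altogether. Kidney injury and LVEF are also followed to day 30, participation runs to day 30 {13}, and {22} requires all adverse events to be registered. The gut is left out of the day-30 lists consistently, so this is a choice and not a contradiction.

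The trial is also described as exploratory {8}, with an intraoperative primary endpoint. That limits the reach of the point but does not remove it for the secondary safety outcomes.

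**Conclusion.** The concern holds in a limited form. As written, day-30 ascertainment rests on hospital electronic records and one visit. Death, disabling stroke or outside readmission that first occurs after discharge may be missed in those who do not attend, and carry-forward, if applied to these outcomes, would count them as event-free. The size of the loss is unknown. At 10% non-attendance it runs from 10% to 36% of visit-dependent events as their relative rate in non-attenders goes from one to five. For death and stroke the effect on the total rate is smaller, because in-hospital events are kept. The expected result is lower event rates and smaller differences between arms, hence a drift towards finding no difference in harm.

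Gastrointestinal ischaemia, one of the three organ harms that the background singles out, has only passive capture after discharge. The primary endpoint and sample size are unaffected. The conclusion assumes that the records are not linked to outside sources and that the full protocol contains no tracing procedure; either would weaken it.

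**What to change.** Amend sections {18b} and {19} of the protocol as follows, with the carry-forward rule also stated in {20c}.

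- Any patient not seen at day 30 is contacted by telephone (patient, relative or general practitioner) about vital status, stroke, dialysis and any admission to any hospital. Where contact fails, vital status is checked in a registry.
- Unknown is recorded separately from no event, and event-free status is not carried forward for day-30 binary outcomes.
- The cause of each re-hospitalisation is recorded, with gastrointestinal ischaemia as a named category.
- Day-30 death is reported for all randomised patients with known vital status, with the number unknown shown by arm.

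The cost is a short call for the minority who do not attend, one or two datasheet fields and a wording change. No extra visit or procedure is needed. Recruitment is planned to 31/12/2026, so remaining patients can be covered prospectively, and vital status can be checked in retrospect for those already past day 30.
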